### Supplementation protocol

Participants will consume either NAC or placebo in a random order according to a double-blind, crossover design. A dosage of 40 mg NAC/kg/day will be administered orally in three doses (equally distributed), in order to maximize cysteine levels (for glutathione synthesis) in the circulation and skeletal muscle, primarily due to NAC fast rate of clearance (~ 6 h post ingestion) [32]. According to a model proposed by Reid in 2001, there is an optimal intracellular redox status required for optimum muscle function and force production [33]. Hence, when NAC is supplemented orally as an exogenous antioxidant (glutathione precursor), under conditions of increased oxidative stress and ROS production, it is plausible to administer a moderate dose for optimal scavenging of ROS, which according to recent studies, represents an absolute dose of ~ 1.2 to 5 g/day and evokes a pronounced improvement in muscle function and performance [34–37]. Larger doses of NAC supplementation may buffer physiological levels of cellular oxidants and may result in impaired muscle force production and performance deterioration [38]. With our dose of 40 mg/kg/day we will reach an absolute dose of approximately ~ 2.8 g of NAC for an average participant weighted ~ 70 kg. Additionally, this dosage has been shown to successfully increase total thiol levels in plasma [39]. NAC in a powder form will be diluted in a 250-ml drink containing 248 ml water and 2 ml of natural, non-caloric, flavoring-sweetener containing sucralose (Flavdrops, My Protein, Cheshire, UK). The placebo supplement will be prepared to be identical to NAC in terms of taste and smell apart from the NAC content. In both trials, each participant will be asked 15 times (once a day) if they realize whether the drink they consumed was the placebo or the experimental one. Responses will be recorded, and correct or incorrect answers will be measured. A research assistant will perform the randomization and assign participants to the interventions (NAC vs placebo) during the clinical trials using an online, computer-based, third-party, semi-automatic randomization system. The same research assistant will have full access to this list and will monitor the presence of any adverse side effects in both trials via questionnaires [30]. Both investigators and participants will be blinded to supplementation condition. Possible adverse reactions to oral NAC supplementation include an upset stomach, nausea, stomach and/or intestinal gas, sleepiness, metallic taste, light-headedness, redness of eye, face, or hands, and cough [39].

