### Muscle strength and soreness

KE maximal eccentric and concentric peak torque of the exercised limb will be measured on an isokinetic dynamometer (Cybex 770, Rosemont, IL, USA) at 60°/s as described elsewhere [45]. DOMS of KE of the exercised limb will be evaluated by palpation of the belly and distal region after participants have performed three full-squat repetitions. Then, participants will rate their soreness level on a scale from 1 to 10 (1 = no pain, 10 = extremely sore). DOMS assessments will be carried out by the same investigator [46].

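### Side effects are monitored by the research assistant who holds the allocation list, so their collection is not blinded at the collector level

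*Protocol article*

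**What the plan says.** All the relevant role assignments stand in the Supplementation protocol section of the protocol article.

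- Randomization: "A research assistant will perform the randomization and assign participants to the interventions (NAC vs placebo) during the clinical trials".
- List custody and side effects: "The same research assistant will have full access to this list and will monitor the presence of any adverse side effects in both trials". The instrument is a questionnaire.
- Blinding: "Both investigators and participants will be blinded to supplementation condition". The research assistant is not named among the blinded.
- Design label: "Participants will consume either NAC or placebo in a random order according to a double-blind, crossover design".
- Expected reactions to oral NAC: these include "upset stomach, nausea, stomach and/or intestinal gas, sleepiness, metallic taste, light-headedness", as well as redness of the eye, face or hands, and cough.

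The section describes no separate blinded collector of side effects and no coding of the list that would keep the assistant from knowing the condition. Elsewhere, the Muscle strength and soreness section says of delayed-onset muscle soreness (DOMS): "DOMS assessments will be carried out by the same investigator".

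**The concern.** Whoever asks about and records side effects should not know which drink the participant is taking. Here the article places the allocation list and the side-effect monitoring with the same person, and says so outright. It is a stated design choice, not a detail that a condensed article left out.

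The expected reactions are mostly symptoms that only the participant can report. Such reports depend on how the question is put, whether a vague answer is followed up, and what is written down. In a crossover each man is assessed under both conditions, and the collector can know which is which each time. At stake is the credibility of whatever the trial reports about the tolerability of NAC against placebo. Differential recording could not be removed afterwards by analysis.

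**Working it through.** No arithmetic applies: the point depends on no rate, effect size or sample size. It was checked by setting the statements side by side.

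1. **Who knows the allocation?** The research assistant randomizes, assigns the interventions and has full access to the list. Nothing in the article masks the list for that person.
2. **Who collects side effects?** The same assistant, in both trials: "will monitor the presence of any adverse side effects in both trials via questionnaires". No one else is given this task.
3. **Who is blinded?** Investigators and participants. From steps 1 to 3, the reporter of a symptom (the participant) is blinded and the collector is not.
4. **Is the measure open to influence?** The six reactions quoted from the section are upset stomach, nausea, gas, sleepiness, metallic taste and light-headedness, all largely or wholly matters of self-report. Redness can be seen and cough can be heard, but an observer who knows the condition can still record these selectively.
5. **By what route would bias enter?** The article does not say whether the questionnaires are self-completed or led by the assistant, nor how often they are given. If they are interviewer-led, prompting and follow-up are both open to influence. If they are self-completed by blinded men, the risk shrinks to clarification, follow-up, transcription and inadvertent disclosure. It becomes smaller but does not vanish.
6. **Which results are touched?** The outcome list in Methods/design names primary, secondary and other outcomes in detail, and adverse effects are in none of the three groups. The Statistical analyses section sets out no comparison of side effects between NAC and placebo. The primary outcomes are muscle-tissue markers and the secondary outcomes are blood markers. DOMS is assessed by an investigator, hence by someone stated to be blinded, and nothing assigns strength testing to the assistant. The weakness therefore bears on tolerability reporting only.

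**The case against.** The strongest reply is that the document is consistent with itself. It says who is blinded, does not include the assistant, and openly gives the assistant the list. A reader might infer that the arrangement contradicts the double-blind claim. It does not, because blinding is defined here as investigators plus participants. This part of the reply stands in full.

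A reader might also infer that an unblinded person is in regular contact with the men, questions them daily about their drink, and so leaks cues that affect soreness ratings and maximal efforts. The article does not support this. It gives no frequency or format for the questionnaires, does not say who asks the daily question about the drink, and places DOMS with a blinded investigator. It also matches the placebo for taste and smell and records the participants' guesses, which would help to detect compromised participant blinding. Spill-over to DOMS or peak torque would need a leak that nothing in the text describes.

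Finally, the present split has one merit: telling symptoms such as metallic taste or facial redness reach only a person who is already unblinded. Handing the questionnaires to an investigator who also rates soreness or strength could weaken the blinding of those outcomes. This stands as a condition on the remedy. It does not justify leaving list custody and side-effect collection in the same hands.

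**Conclusion.** The point holds in a limited form. Side-effect collection is unblinded at the collector level by the article's own role assignment, and no safeguard is described. This can bias a NAC-versus-placebo tolerability comparison.

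The size cannot be quantified from the document. The coverage is complete, since all the side-effect monitoring described in both trials goes through this assistant, but that says how many records are exposed and not how far they are biased. The direction is also not determined, although knowledge of the expected NAC reactions makes fuller recording under NAC plausible.

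The conclusion assumes that the list shows the actual condition, as the wording on full access implies. How serious it is depends on how the questionnaires are administered, which the article does not state. The trial's listed outcomes are not called into question by this point.

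**What to change.** Separate the two roles. The holder of the allocation list should neither administer nor record the side-effect questionnaires. A team member without access to the list, who does not assess DOMS or strength, should collect standardised forms that participants complete themselves, with the same form and timing in both trials.

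The Trial status section says that the trial has not yet commenced, so the change can be made before any side-effect data are collected. It leaves the randomization, the sample size and the listed measurements as they are. The cost is a reallocation of tasks; the article does not describe staffing, so it is an assumption that the existing team can absorb it. A residual downside is that reported symptoms may hint at the condition to the new collector, which is why that person should have no part in assessing soreness or strength.

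If the roles cannot be separated, use self-completed forms, limit the assistant's part to receiving them, and state in the protocol and the report that side-effect monitoring was not blinded.

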
### Anthropometric measurements

Standing body mass and height will be measured on a beam balance equipped with stadiometer (Beam Balance-Stadiometer, SECA, Vogel & Halke, Hamburg, Germany) while participants wear light clothing as described previously [40]. BMI will be calculated as mass per height squared. Dual energy X-ray absorptiometry (DXA) scanner (GE Healthcare, Lunar DPX-NT, Singapore) will be utilized for body composition assessment. On each testing day the equipment will be calibrated using a LS phantom in accordance to standard procedures. Participants will be asked to remain still and they will be scanned in the supine position using the total body analysis under scanning conditions automatically selected by the software (standard, thick, thin scanning). Total and regional fat mass (g), lean mass (kg) and body fat (% and kg) values will be obtained. GE enCORE software will be utilized for all DXA scans and analyses.

### Resting metabolic rate

For RMR assessment, resting VO_2_/VCO_2_ values will be measured in the morning (07:00–09:00) after overnight fasting utilizing an open-circuit type indirect calorimeter with a ventilated hood system (Vmax Encore 29, BEBJO296, Yorba Linda, CA, USA) and the 24-h RMR will be calculated as previously described [41].

### Physical activity assessment

Habitual PA will be monitored over a 7-day period using the ActiGraph, GT3X+ accelerometers (ActiGraph, Pensacola, FL, USA). Participants will be taught, by an experienced researcher, how to wear the adjustable belt on the waist with the accelerometer monitor on the right side of the hip and they will be asked to wear it throughout the day for seven consecutive days, apart from bathing, swimming and sleeping. To be included in the analysis, participants will have to complete four full days of wearing time (i.e., ≥ 4 days with ≥ 10 wear hours/day). From the data obtained, non-wear time will be calculated and daily activity levels and sedentary time will be expressed as steps per day and time spent at sedentary, light, moderate, vigorous and moderate-to-vigorous PA [42, 43]. ActiLife 6 software will be used to initialize accelerometers and download data using a 60-s epoch length.

### Dietary intake analysis

Participants will be instructed by a registered dietitian on how to estimate food/fluid servings and sizes and how to complete a 7-day diet recall before and during both trials and the washout period to ensure that they will follow the same dietary regimen. Specifically, participants will be provided with colored images showing different food portions and detailed instructions that they will use to weight their food. When possible, the name of the brand and/or manufacturer will be recorded. Diet recalls will be analyzed using the Science Fit Diet 200 A (Science Technologies, Athens, Greece) dietary software for data regarding total energy (kcal), carbohydrate, fat, protein (g/kg/day and g/day), vitamin A (mg/day), vitamin C (mg/day), vitamin D (IU/day), vitamin E (mg/day), selenium (mg/day), zinc (mg/day) and magnesium (mg/day).

### Maximal oxygen consumption

VO_2max_ will be measured using open-circuit spirometry with an automated pulmonary gas exchange system (Vmax Encore 29, BEBJO296, Yorba Linda, CA, USA) via the breath-by-breath analysis during a graded exercise test on a treadmill (Stex 8025 T, Daegu, Korea) until volitional fatigue, according to procedures previously described [44]. Briefly, following a standard warm-up (8 min of low-intensity running on a treadmill) each participant will complete a graded exercise test protocol at a starting speed of 8–10 km/h (depending on participants’ fitness training history), with an increase of 1 km/h in the running speed every 2 min. During the test VO_2_/VCO_2_ values will be measured in 20-s intervals. Criteria for terminating the test include: (1) participant reached a level of volitional fatigue, (2) predicted maximum heart rate reached and/or surpassed, (3) respiratory quotient values ≥ 1.10 and (4) plateau in VO_2_ values. VO_2max_ will be calculated from the averaged VO_2_ measures during the final minute of the test.

### Muscle strength and soreness

KE maximal eccentric and concentric peak torque of the exercised limb will be measured on an isokinetic dynamometer (Cybex 770, Rosemont, IL, USA) at 60°/s as described elsewhere [45]. DOMS of KE of the exercised limb will be evaluated by palpation of the belly and distal region after participants have performed three full-squat repetitions. Then, participants will rate their soreness level on a scale from 1 to 10 (1 = no pain, 10 = extremely sore). DOMS assessments will be carried out by the same investigator [46].

### Blood sampling and biochemical assays

Following an overnight fasting blood samples will be drawn from the antecubital vein by venipuncture with a 20-gauge disposable needle equipped with a Vacutainer® tube holder (Becton Dickinson, Franklin Lakes, NJ, USA) with the participants in a supine position. For serum separation, blood samples will be allowed to clot at room temperature and then will be centrifuged (1370 g, 10 min, 4 °C). The supernatant will be aliquoted into eppendorf tubes for subsequent analysis of CRP, TNF-α, IL-6, IL-8, IL-10 (inflammation), CK activity (muscle damage), TAC (oxidative stress) and cortisol (hormonal response). Another blood portion will be collected in ethylenediaminetetraacetic acid (EDTA)-containing tubes and will be centrifuged at 1370 g, 10 min, 4 °C to collect the plasma. Plasma samples will be used for the measurement of PC (protein oxidation) and MDA (lipid peroxidation). Packed erythrocytes (RBCs) will be obtained after lysis of the plasma samples for the measurement of GSH, GSSG, CAT and Hb (RBCs’ redox status). All samples will be aliquoted in multiple eppendorf tubes and stored at − 80 °C until analysis. A small portion of whole blood (~2 ml) will be collected in tubes containing EDTA for a complete blood count analysis on an automated hematology analyzer (Mythic 18, Orphee SA, Geneva, Switzerland). All assays will be performed in duplicate.

### Muscle biopsy sampling

Percutaneous needle muscle biopsies will be obtained after an ~ 10 h overnight fast (baseline) using the Bergstrom technique with the application of manual suction, from the mid-portion of the vastus lateralis muscle under local anesthetic (xylocaine 1%), by a registered surgeon [47]. After the biopsy, no antibiotics, pain killers or anti-inflammatory drugs will be administered to participants. Volunteers who will receive any type of pharmaceutical drugs and/or analgesics in the biopsy site, in the rare case of excess bleeding or pain, will be excluded from the analyses. Subjects will be asked to refrain from any PA at least 96 h prior to muscle biopsy sampling. Subsequent muscle biopsies (pre exercise, 2 and 8 days post exercise) will be spaced 5 cm apart to diminish a repeated biopsy effect. Upon excision, adipose tissue and blood will be carefully removed and muscle samples suited for histology will be aligned and immediately be mounted in optimal cutting temperature (OCT) compound, immersed in nitrogen-cooled isopentane and stored at − 80 °C. Embedded samples will be sectioned (7 μm) at − 20 °C using a cryostat, placed on glass slides and stored at − 80 °C. Muscle samples suited for mRNA, Western blotting, muscle thiols and OXS analyses will directly be frozen in liquid nitrogen, and stored at − 80 °C.

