## Methods/design

### Study overview and design

The methods and ethics of the present study have been approved by the Institutional Review Board of the University of Thessaly (ref. number 1387) and procedures are in accordance with the Declaration of Helsinki, as revised in 2013. The SpEED study incorporates a randomized, two-trial (NAC vs placebo), cross-over, double-blind, repeated-measures design. Participants who will fulfill the inclusion criteria will have their body mass, height, resting metabolic rate (RMR), body composition, muscle strength, soreness and maximal oxygen consumption (VO_2max_) measured. Since protein and antioxidant consumption as well as systematic physical activity (PA) and/or exercise may affect SCs responses and/or redox status, participants’ daily nutrient intake (via a 7-day diet recall with emphasis on protein and antioxidant intake) and PA levels (via accelerometry instrumentation) will be monitored for a week before the inception of the study [24–26]. Then, a 2-week adaptation period (only before the first trial) will be applied to adjust (through a balanced diet, using RMR values and daily energy expenditure measurements) protein and antioxidant intake at the levels required by current Recommended Dietary Allowances (RDAs) (0.8–1 g of protein/kg/day; 900 mg/day of vitamin A; 90 mg/day of vitamin C; 600 IU/day of vitamin D; 15 mg/day of vitamin E; 11 mg/day of zinc; 400 mg/day of magnesium and 55 mg/day of selenium) [27, 28]. This dietary protocol will be designed and implemented by a registered dietician. During the same time-frame, familiarization with experimental procedures will be provided.

Evidence exists that skeletal muscle growth and myogenic potential is directly related to its basal SCs content [24, 29]. As such, volunteers will provide a resting (they will abstain from any exercise or intense PA for at least 5 days prior to sampling) muscle biopsy sample (baseline sampling) from their vastus lateralis muscle (of their dominant limb) and based on its SCs content will be stratified to either high (HR) or low (LR) respondents. Participants will be stratified as HR or LR using a K-means cluster analysis. Blood sampling and performance measurements will also be performed at baseline.

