Following stratification to the HR and LR groups, volunteers of each group will then perform two trials in a randomized order: (1) NAC ingestion and (2) placebo ingestion. NAC or placebo will be consumed before (a 7-day loading phase) and after (immediately post exercise and for eight consecutive days thereafter) an intense eccentric exercise protocol. During both trials, participants will follow the balanced daily dietary protocol of the adaptation period. However, daily dietary intake will be recorded and analyzed during each trial in an attempt to minimize deviations from the prescribed diet. A 4-week washout period will be implemented between trials (dietary intake during this period will also be adjusted according to that applied during the adaptive period). During the entire experimental period, participants will be asked to abstain from any strenuous PA or exercise. Muscle biopsies and blood samples will be collected after overnight fasting before the exercise protocol (pre-exercise sampling) as well as at 2 and 8 days post exercise. Muscle strength and delayed onset of muscle soreness (DOMS) will be evaluated at the same time points. All measurements and collection of biological samples will be performed at the same time of day, in both trials, to prevent circadian rhythm variations. Figure 1 shows the Consolidated Standards of Reporting Trials (CONSORT) diagram of the study and Fig. 2 illustrates the experimental flowchart for the clinical trials.

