### Statistical analyses and Power calculation

A preliminary power analysis (based on previous studies that used NAC administration to investigate its effects on EIMD), using the G*Power 3.0.10 program, showed that a minimum number of 10 participants per group is needed to obtain statistical meaningful results among repeated measurements [30]. Specifically, power calculation was performed for a two-way repeated-measures analysis of variance (ANOVA), within-between interaction test and input variables included: effect size, 0.55; α error, 0.05; power, 0.95; number of groups (LR and HR), 2; correlation among repeated measures, 0.5 and non-sphericity correction, 1. However, the total number of participants depends also on potential dropouts according to the following formula: *n* ’  = n/(1 − d) [55].

Thus, the final number of participants to be recruited with a dropout rate of 15% would be *n*’ = 10/(1–0.15) = 11.8. Therefore, ≥ 12 participants per group (LR vs HR) will be selected from the initial sample (*N* = 40–60) via k-means clustering to participate in the clinical trial (NAC vs placebo).

A k-means cluster analysis will be utilized to efficiently define two separate groups of subjects (LR and HR groups) from the total sample (*N* = 40–60), based on the SCs content of their vastus lateralis muscle of their dominant leg [24]. This type of analysis requires a relatively large initial sample size (*N* = ≥ 40), is a form of partitional clustering and is a multivariate method used to identify homogeneous groups (i.e., clusters) of cases based on a common trait [29, 56].

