All analyses and reporting of the results will comply with the Standard Protocol Items: Recommendations for Interventional Trials (SPIRIT) Statement for reporting randomized clinical trials (RCTs) [57]. Results of participant’s baseline characteristics and outcome variables (primary, secondary and other) will be summarized using descriptive statistics and will be expressed as mean (standard deviation) or median (range) for continuous variables. Data normality will be examined using the Kolmogorov-Smirnov and the Shapiro-Wilk tests. If our data sets follow normal distribution, parametric tests will be applied. Baseline comparisons on the LR and HR groups (anthropometrics, body composition, strength, VO_2max_, dietary profile, PA) will be performed using a one-way ANOVA test. Time- and trial-effect comparisons within and between trial (NAC or placebo) in the LR and HR groups will be analyzed using a two-way repeated-measures ANOVA test with a Bonferroni correction for pairwise comparisons. If the data normality is violated, non-parametric tests will be applied. Baseline comparisons on the LR and HR groups will be performed using a Kruskal-Wallis test. Time-effect comparisons within trial (NAC or placebo) in the LR and HR groups will be analyzed using a Friedman test accompanied by Wilcoxon signed-rank test for pairwise comparisons. Trial-effect comparisons between trials (NAC vs placebo) in the LR and HR groups will be analyzed using a Kruskal-Wallis test accompanied by a Mann-Whitney *U* test for pairwise comparisons. Pearson’s correlation analysis will also be used to examine possible relations among variables. Correlation coefficients of r < 0.2, 0.2 < r < 0.7 and r > 0.7 will be defined as small, moderate and high, respectively. The level of statistical significance will be set at *p* < 0.05. Effect sizes (ES) and confidence intervals (95% CI) will be calculated on results of all dependent variables using the Hedge’s *g* method, corrected for bias. ES will be interpreted as none, small, medium-sized and large for values 0.00–0.19, 0.20–0.49, 0.50–0.79 and ≥ 0.8, respectively. Multiple-imputation analysis will also be utilized to handle missing data during data collection and sensitivity analyses will be executed to evaluate the robustness of the results [58]. Statistical analyses will be performed using the SPSS 20.0 software (IBM Corp., Armonk, NY, USA).

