## Discussion

The present study is designed to assess the impact of redox status on SCs responses and the mechanisms (hormonal regulation, M1 and M2 macrophages, intracellular signaling) associated with their mobilization and function following aseptic skeletal muscle trauma induced by exercise. Nutritional supplementation or medications have been shown to affect SCs biology under traumatic conditions. Hydrolyzed whey protein supplementation and anti-inflammatory medication (ibuprofen) results in increased SCs response and expedites skeletal muscle recovery [25, 48]. Antioxidant supplementation (vitamin C, vitamin E, NAC or combined antioxidants) may attenuate loss of muscle force production and reduce muscle soreness and lipid peroxidation levels but it may also delay recovery suggesting a potential redox-associated mechanism involved in muscle healing [54, 59]. However, this possibility has not been explored in the human skeletal muscle. More specifically, there is no information regarding the redox-dependent mechanism of SCs mobilization and action in human skeletal muscle. It is well established in the literature that thiol oxidation is a major post-translational oxidative modification affecting the cysteine residues in multiple proteins [60]. On the other hand, increased ROS can oxidize GSH leading to irreversible modification [61]. In this sense, low levels of GSH may not only attenuate the antioxidant defense leading to SCs damage but it may also alter cellular redox status drastically. Furthermore, SCs activity is also determined by redox-sensitive cues (cytokines, immune cells, signaling molecules) emerging from the surrounding microenvironment [62]. Supplementation with a powerful GSH precursor, such as NAC, could not only foster GSH levels and thus muscle’s antioxidant potential but also will change myofiber redox balance which is crucial for the redox-dependent regulation of intracellular signaling pathways mediating pro- and anti-inflammatory response to muscle trauma [30]. Our research hypothesis states that NAC-induced change of muscle’s redox status will upregulate SCs availability and mobility under conditions of increased oxidative stress and inflammation in human skeletal muscle. This is of great importance as muscle injury is present in several clinical conditions characterized by increased muscle wasting, atrophy and sepsis that result in physical deterioration and poor quality of life such as in many types of cancer, cachexia, muscular dystrophies, etc. [11, 12]. Consumption of NAC, a potent thiol-based antioxidant, upregulates GSH/GSSG and reduces the respiratory burst and MAPK- and NF-kB-mediated pro-inflammatory cytokine release during inflammation produced by muscle injury [30, 63]. Information derived from this study will elucidate the redox-dependent regulation of intracellular signaling pathways involved in SCs regulation and muscle healing in human skeletal muscle. Therefore, the results of the proposed study should provide information about possible nutritional and/or pharmaceutical interventions to promote SCs function and increase skeletal muscle’s healing potential.

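### Medication for biopsy-site pain or bleeding removes the whole volunteer from the analyses, including data the drug could not have affected

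*Protocol article*

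**What the plan says.** The rule is in Muscle biopsy sampling. Its subject is the volunteer who receives a drug or analgesic at the biopsy site, and such volunteers, "in the rare case of excess bleeding or pain, will be excluded from the analyses". No event rate is given beyond the word rare.

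Study overview and design gives the timing. A baseline biopsy comes first, and each man "based on its SCs content will be stratified to either high (HR) or low (LR) respondents". After that, "volunteers of each group will then perform two trials in a randomized order". Within each trial, biopsies are taken "before the exercise protocol (pre-exercise sampling) as well as at 2 and 8 days post exercise", and the pre-exercise one follows a 7-day loading phase. A 4-week washout separates the trials.

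The Discussion says that antioxidant supplementation, NAC among the examples, "may attenuate loss of muscle force production and reduce muscle soreness and lipid peroxidation levels". It also says that an anti-inflammatory drug (ibuprofen) increases the satellite-cell response.

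Statistical analyses and Power calculation has a missing-data plan: "Multiple-imputation analysis will also be utilized to handle missing data during data collection", with sensitivity analyses for robustness. It does not link that plan to the biopsy rule.

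**The concern.** The reason for the rule is sound: a drug that changes the satellite-cell response could contaminate a primary outcome. The unit of exclusion is the problem. The contamination belongs to particular samples, but the rule removes the person.

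Two things follow. First, data that the drug could not have reached are thrown away, in a trial with about 12 men per group and invasive samples that cannot be repeated. Second, the exclusion acts after randomization on an event that may be related to treatment and to response. If men with more post-exercise pain are more likely to be medicated, the analysed set tilts towards milder responders. If NAC lowers that pain, the event would occur more often in the placebo trial, possibly in men whose NAC-placebo difference is larger than average.

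**Working it through.** **Which biopsies are affected.** One baseline biopsy precedes randomization, and an exclusion there does not raise this concern. After randomization there are 3 biopsies per trial × 2 trials = 6, all after loading has begun in that trial. Four of the six (days 2 and 8, both trials) follow the eccentric exercise and two precede it.

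**How much unexposed data the rule drops.** A drug given because of a biopsy can affect only later samples. If it is given in the second trial, the first trial is already complete. If it is given in the first trial, I assume that the 4-week washout clears it.

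| Biopsy that led to the drug | Samples exposed | Samples dropped | Unexposed samples dropped |
|---|---|---|---|
| Pre-exercise | 2 (days 2 and 8) | 6 | 4 |
| Day 2 | 1 (day 8) | 6 | 5 |
| Day 8 | 0 | 6 | 6 |

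If the three occasions are equally likely (an assumption), the mean number exposed is (2 + 1 + 0)/3 = 1 of 6, so on average 5 of the 6 samples dropped are unexposed.

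**Whether the trigger may depend on treatment.** The Discussion's statement concerns muscle soreness and antioxidants in general, NAC included. The exercise is performed with the quadriceps, the biopsies come from the vastus lateralis, and soreness of the exercised knee extensors is itself measured (Muscle strength and soreness). A link from soreness to biopsy-site pain on days 2 and 8 is a reasonable inference. The document offers nothing comparable for bleeding, and the inference is weaker for the pre-exercise biopsies, when there is no exercise damage yet in that trial.

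**What this does to the comparison.** Removing a man removes both his NAC and his placebo data, so the contrast remains within person and no imbalance between arms arises.

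**Sample size.** The plan's figure reproduces: n' = 10/(1 − 0.15) = 11.76 (given as 11.8), rounded up to at least 12 per group. After 15% dropout, 12 × 0.85 = 10.2 are expected, which is 0.2 above the stated minimum of 10. The chance of fewer than 10 analysable out of 12 in one group is already 0.26 from that dropout alone. If biopsy exclusions at an assumed rate q come on top, the expected number is 12 × 0.85 × (1 − q):

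| q (assumed) | Expected analysable of 12 | Chance of fewer than 10 |
|---|---|---|
| 0 | 10.2 | 0.26 |
| 2% | 10.0 | 0.32 |
| 5% | 9.7 | 0.42 |
| 10% | 9.2 | 0.56 |

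For orientation, an assumed independent risk r per biopsy gives 1 − (1 − r)^6 per man: 3.0% at r = 0.5%, 5.9% at 1% and 11.4% at 2%.

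**Power if a few men are lost.** The inputs are effect size f = 0.55, α = 0.05, correlation ρ = 0.5 and two groups. The number of measurements m is not listed, so I tried 2, 3, 4, 6 and 8. With noncentrality λ = f²·N·m/(1 − ρ) for the within-between interaction, power at N = 16 in total is at least 0.983 (the lowest is at m = 2, where λ = 0.3025 × 16 × 2/0.5 = 19.36). Definitions that leave out the stated correlation give less: λ = f²·N·(m − 1) with m = 4 gives 0.946 at N = 20 and 0.877 at N = 16.

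**The case against.** **The rule protects a primary outcome.** The document itself says that an anti-inflammatory drug alters the satellite-cell response, and its eligibility criteria bar such drugs. This stands, and it is why exposed samples should not simply enter the primary analysis. It justifies removing those samples, not the man's unexposed ones.

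**The event is rare and the treatment link is inferred.** Both are true. The Discussion's wording is hedged, concerns soreness rather than needle-site pain, and says nothing on bleeding. Selection is therefore a possibility whose size cannot be estimated. The loss of unexposed data needs no such inference.

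**Multiple imputation is already planned, and an unseen analysis plan may connect it to this rule.** It may. But the article states an exclusion of volunteers, and imputation cannot recover men who are out of the analyses.

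**A stronger reading to resist.** A reader might infer that the rule uses up the sample-size margin and takes the groups below 10. The documents do not show this. No event rate is given, 12 is a floor, and the allowance in "the final number of participants to be recruited with a dropout rate of 15% would be" is not itemised and may already cover such losses. The 0.2-person surplus is a product of rounding up, so almost any extra loss would cross it. With the formula that uses the stated correlation, power stays above 0.95 even at 16 men in total. A reader might also infer bias between arms, and the pairing rules that out.

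**Conclusion.** The concern holds for the six post-randomization biopsies. As written, the rule excludes a randomized person because of a post-randomization event, and each time it discards four to six samples that the drug could not have affected. That count assumes that the washout clears the drug when it is given in the first trial. Where the trigger is pain after the exercise, the rule may also select milder responders. That part is an inference, and its direction and size are not established.

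On sample size, it can be said only that the margin is thin (10.2 expected of 12 after 15% dropout) and that further exclusions may reduce it. This is a correction that should be made. It is not a flaw that invalidates the design.

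**What to change.** Replace the volunteer-level exclusion with a sample-level one:

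- Keep every randomized participant in the analyses.
- In the primary analysis, set to missing only the samples taken after the drug within that trial. Retain the sample whose biopsy led to the drug, all earlier samples and the other trial.
- Handle the missing values with the multiple imputation already planned. Soreness is recorded at the same time points, so scores obtained before the drug can inform the imputation.
- Run two sensitivity analyses: one that includes the exposed samples as observed, and one that applies the whole-volunteer exclusion now in the protocol.
- Report the number of such events under NAC and under placebo, and by time point.

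If the authors meant the affected sample all along, the wording change alone settles the main point. The cost is a sentence or two in the protocol, some imputation and two extra runs. Trial status says that the trial has not commenced, so the change can be made before any outcome data exist. Clinical management after a biopsy is not affected.
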